## Abstract

**Background:**

Malnutrition among school children may contribute to adverse health consequences such as non-communicable diseases, poor cognitive performance, psychological distress and poor quality of life that may persist into adulthood. In order to prevent childhood malnutrition, an intervention programme that integrates nutrition education and healthy school food environment is needed to provide nutrition information and reinforce the skills on healthy eating behaviours in schools. This paper describes a study protocol of a school-based intervention programme that integrates nutrition education and healthy school food environment, namely School Nutrition Programme (SNP). The SNP is a primary prevention programme that promotes healthy lifestyle among primary school children in light of the high prevalence of malnutrition in Malaysian children.

**Methods/design:**

This quasi-experimental study aimed to evaluate the effectiveness of the SNP between intervention and comparison groups before and after the SNP, and after a 3-month follow-up. The SNP consisted of two main components, whereby three nutrition education sessions were implemented by trained teachers using three standardised modules, and healthy school food environment was implemented by the canteen food handlers with the provision of healthy menu to children during school recess times. Children from intervention group participated in the SNP, in addition to the standard Physical and Health Curriculum. The comparison group attended only the standardised Physical and Health Curriculum and the school canteen food handlers were reminded to follow the standard canteen guidelines from the Ministry of Education Malaysia. The assessment parameters in evaluating the effectiveness of the programme were knowledge, attitude and practice on nutrition, eating behaviours, physical activity, body composition, psychological distress, cognitive performance and health-related quality of life. Assessments were conducted at three time points: pre-intervention, post-intervention and 3-month follow-up.

**Discussion:**

It was hypothesised that the SNP would be effective in promoting healthy lifestyle among school children, and further contributes in preventing malnutrition problem, enhancing cognitive performance and improving health-related quality of life among school children. Findings of the present study can be expanded to other schools in future on ways to improve nutrition education and healthy school food environment.

**Trial registration:**

UMIN Clinical Trial Registration UMIN000032914 (Date of registration: 7th June 2018, retrospectively registered).

**Protocol version:**

16th September 2019 & Version 4

## Background

The World Health Organization reported that 151 million and 51 million children under 5 years of age were stunted and wasted respectively; on the other hand, the number of overweight or obese children under the age of five was 38 million in 2017 globally [1]. More than half of stunted children, more than two thirds of wasted children and almost half of overweight children lived in Asia [2]. In South-East Asia, at least one in every four children under five was stunted; at least one in every 10 children under five was wasted and overweight respectively [2].

Overnutrition and undernutrition coexist among primary school children in Malaysia [3–6]. The National Health and Morbidity Survey (NHMS) 2017 showed that the prevalence of overnutrition (overweight 16.3%; obesity 17.4%) were two times higher than undernutrition (thinness 6.7%; stunting 7.8%) among Malaysian children aged 10 to 12 years [7]. In addition, the prevalence of overnutrition among primary school children (33.7%) was higher than secondary school adolescents (28.5%) [7]. Malnutrition refers to deficiencies, excesses or imbalances in a person’s intake of energy and/or nutrients [8]. Undernutrition may increase risks of impaired physical and cognitive performance, as well as morbidity and mortality during childhood [9, 10]. On the other hand, overnutrition is associated with increased risks of psychological distress such as depression, anxiety and social withdrawal [11–13]; low self-esteem, poor quality of life and cognitive deficits, especially in executive function [14, 15]. In order to achieve the Sustainable Development Goals, it is important to recognise the role of prevention and health promotion in order to reduce the prevalence and the burden of diseases [16]. Therefore, designing an effective healthy lifestyle programme that is interconnected with the education programmes in primary school can improve health literacy that is needed to prevent this public health concern among primary school children.

In Malaysia, children aged 7 to 12 years old are generally enrolled in primary school levels for 6 years, which is known as Standards 1 to 6 [17]. Lifelong nutritional patterns are formed during childhood, which can reach at influential stages in their lives [18, 19]. Previous studies reported that Malaysian primary school children are at increased risk of poor dietary behaviours, including breakfast skipping, low fruits and vegetables intakes, unhealthy snacking behaviours and low physical activity [7, 20, 21], which may affect their nutritional status and expose children to malnutrition [22, 23], lower cognitive performance and poor quality of life [24–26]. There is a need to have a holistic nutrition intervention programme that promotes healthy eating and active living for all primary school children, so that they can have a healthy lifestyle, good nutritional status, better cognitive performance and good quality of life.

This paper describes the protocol of School Nutrition Programme (SNP) that consisted of two main components, namely nutrition education and healthy school food environment. The present study aimed to evaluate the effectiveness of SNP on differences in primary outcome measures including anthropometric measurements, knowledge, attitude and practice on nutrition, eating behaviours, physical activity; and secondary outcome measures including psychological distress, cognitive performance and health-related quality of life among primary school children. A process evaluation was focused on the attendance rate of children during the School Nutrition Campaign, teachers and canteen food handlers during training of trainers; and the programme feedbacks from children, teachers and canteen food handlers after the study.

## Methods/design

### Study design

The present study design was a quasi-experimental design. Out of 147 National Primary Schools in Batu Pahat district, a total of 143 National Schools met the inclusion criteria of being co-educational, non-religious, non-special educational, multi-ethnic and government funded schools. Then, these 143 schools were stratified based on the three main school types, namely i) National Primary School (SK), ii) National Chinese Primary School (SJKC) and iii) National Tamil Primary School (SJKT). Two schools from each stratified group were selected. One school was selected as Intervention Group (IG) and one as Comparison Group (CG) from each school type. All children from these selected schools were invited to participate in the study.

### Participants

This study was conducted in six selected schools in Batu Pahat District, Johor State, Malaysia. School authorities (principal and teachers) and canteen food handlers from three selected intervention schools were invited to participate in the study. All Malaysian children (males and females) who were enrolled in Standards 1 to 5 (aged 7 to 11 years) and who was either Malay, Chinese or Indian were invited in the study (Fig. 1). Upon request from the Ministry of Education (MOE) Malaysia, children in Standard 6, who would be attending the National Primary School Evaluation Test, were excluded from the study. In addition, children with learning disorders, obvious genetic disorders such as attention deficit hyperactivity disorder (ADHD) were excluded from the study. The children were assessed prior to the start of the programme (Pre-Intervention), one-week right after completing SNP (Post-Intervention I) and three-month follow-up without intervention (Post-Intervention II).

**Fig. 1 Fig1:**
[figure not shown]
Children’s flow diagram

### Sample size calculation

The sample size for primary school children was calculated using Aday’s (2006) equation [27]. Based on a previous study in Malaysia, the mean difference of waist circumference between intervention and comparison group after the intervention programme was taken into consideration to calculate the sample size of the SNP [28].
$$ \mathrm{n}=\frac{2{\upsigma}^2{\left[{\mathrm{Z}}_{1\hbox{-} \upsigma /2}+{\mathrm{Z}}_{1\hbox{-} \upbeta}\right]}^2}{{\left({\upmu}_1\hbox{-} {\upmu}_2\right)}^2} $$

Based on the study, the mean change in waist circumference for intervention group after the intervention programme was 0.1 cm, whereas mean change in waist circumference for comparison group after the intervention programme was 2.2 cm. The calculated sample size was 195 children in intervention and comparison groups, respectively. The sample size was also adjusted for a response rate of 80.0%. The intended sample size was 488 primary school children from Standards 1 to 5 in Batu Pahat District. Considering a power of 80% and a level of significance of 5%, a total of 244 children was needed for each intervention and comparison group, respectively. The small effect size of 0.09 was obtained.

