### Data analysis

The evaluation of the study was based on the modified intention-to-treat analysis to retain children in the study [44]. Children who fulfilled the following criteria would be included in the data analysis process:
i.Children of the intervention group who have attended at least two camps in the School Nutrition Programmeii.Children from both the intervention and comparison groups who had completed Pre-Intervention, Post-Intervention I and Post-Intervention II.

All statistical analysis will be conducted using IBM SPSS statistics 24.0. Descriptive analysis such as frequency and percentages, will be reported for categorical variables, while means and 95% confident interval will be reported for continuous variables. Skewness test of normality will be used to assess the normality of continuous variables. A value of skewness within the range of ±2.0 will be considered as normally distributed [45]. The Chi-square Test or Fisher’s Exact Test will be used to determine the association between two or more groups of categorical variables. The Independent sample t-test will be used to compare the mean values of the continuous variables between intervention and comparison groups and Paired sample t-test will be used to compare the mean values at pre-intervention and post-intervention within the intervention and comparison groups.

Simple linear mixed model will be conducted to determine the association of each covariate (such as time, group, child’s age, parental education level and school type) with all the dependent variables (namely knowledge, attitude and practice on nutrition, eating behaviour, physical activity, anthropometric measurement, psychological distress, cognitive performance and health-related quality of life). Multiple linear mixed model will be conducted to investigate the dependent variables between groups (intervention and comparison) over time, adjusted for covariates. Interaction term of time and group will be included in the model. The differences in all continuous variables between intervention and comparison groups will be determined at three time points (Pre-Intervention, Post-Intervention I and Post-Intervention II). The statistical significance will be set at *p* < 0.05. The data will be stored for future use after the completion of the study.

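### The single 80% response rate does not say which losses it covers, and the completer and two-camp rule discards children the planned mixed model could use

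*Protocol article*

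**What the plan says.** In the protocol article, Sample size calculation, the base figure rests on a difference in mean change in waist circumference: "The calculated sample size was 195 children in intervention and comparison groups, respectively". One allowance follows: "The sample size was also adjusted for a response rate of 80.0"%. The section then concludes: "Considering a power of 80% and a level of significance of 5%, a total of 244 children was needed" in each group, 488 in total. No other allowance is named. The section does not say whether a response means agreeing to take part or supplying complete data, or whether 488 counts children approached or children enrolled.

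The Data analysis section describes the analysis as modified intention-to-treat, with the aim of retaining children. It sets two conditions for inclusion:

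- intervention children must be those "who have attended at least two camps";
- children in both groups must be those "who had completed Pre-Intervention, Post-Intervention I and Post-Intervention II".

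The same section plans a linear mixed model over the three time points with a time-by-group interaction. According to the Participants and Measurements sections, the assessments fall before the programme, one week after it, and three months later. With a three-month programme, that is about six months in all.

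**The concern.** The power statement and the analysis set are both fixed in print, but nothing connects them. The 80% power belongs to 195 analysed children per group. Whether the plan can be expected to deliver that number depends on what the 20% margin is for. If refusals use it up, the completer rule and the camp rule have no allowance behind them. If it covers loss after entry, refusals have none, although that matters only if 244 is the number approached.

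The exclusion rule matters more. A likelihood-based mixed model uses the records a child has, so requiring all three assessments gives up information that the planned model would use. The camp rule applies in one arm only. Intervention children with poor attendance are removed, while comparison children who would have attended poorly stay in. The compared groups then differ by a condition tied to engagement, which can bias the estimate as well as shrink the sample.

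**Working it through.** **Inputs.** From Sample size calculation: two-sided 5% significance, 80% power, mean changes of 0.1 cm and 2.2 cm (difference 2.1 cm), 195 per group, 80% response rate, 244 per group. The documents give no SD and no loss rate. The SD is therefore back-solved, and the loss rates below are assumptions.

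**1. The plan's inflation.** 195 / 0.80 = 243.75, rounded up to 244 per group; 2 × 244 = 488. Both figures are reproduced.

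**2. Implied SD.** From n = 2·SD²·(1.960 + 0.842)² / 2.1² with n = 195, SD = 7.40 cm, so d = 2.1 / 7.40 = 0.284. The 195 itself cannot be checked independently.

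**3. Power by number analysed.** Power = Φ(d·√(n/2) − 1.960), ignoring clustering:

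| Loss after entry (assumed) | 195 per group enter: analysed | Power | 244 per group enter: analysed | Power |
|---|---|---|---|---|
| 0% | 195 | 80.0% | 244 | 88.0% |
| 10% | 175.5 | 75.7% | 219.6 | 84.4% |
| 20% | 156 | 70.7% | 195.2 | 80.0% |
| 30% | 136.5 | 65.0% | 170.8 | 74.6% |

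If 244 per group enter, 80% power is kept up to a loss of 1 − 195/244 = 20.1%.

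**4. Extra loss from the camp rule.** With 10% loss in the comparison group and 20% in the intervention group, power is 73.2% (195 enter) or 82.2% (244 enter). With 20% and 30%, it is 67.8% or 77.3%.

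**5. Covering both kinds of loss.** With 80% participation and 10% later loss, 195 / (0.80 × 0.90) = 270.8, so 271 per group would have to be approached. With 20% later loss, 195 / (0.80 × 0.80) = 304.7, so 305. Both exceed 244.

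**6. Three visits or two.** If 195 are those who entered, a missed baseline overlaps with non-participation, so only the two later visits should count as further loss. Assumed independent completion of 95%, 93% or 90% per visit then leaves 0.95² = 90%, 0.93² = 86% or 0.90² = 81%. Cubing these rates would overcount.

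**The case against.** A reader might infer that the stated 80% power holds only if no child is lost. The documents do not support that. The sample size section speaks of 244 children needed in each group, which can equally mean 244 enrolled. On that reading, the margin covers about 20% loss, and power without loss is 88%. The Study design section also says that all children in the selected schools were invited. Invitation was not capped at 244 per group, so refusals need not reduce entry to 195. The flow diagram is not shown and cannot settle the matter.

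The arithmetic from 195 to 244 is correct, and a condensed article may leave the definition of an inflation factor to the full protocol. The loss rates are assumed, and the SD is back-solved. All these points stand, and they remove any unconditional claim of a power shortfall.

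They do not rescue the exclusion rule. It is printed as the analysis set, it works against the stated aim of retaining children, and it imposes a one-arm attendance condition whichever reading of the 80% is right.

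**Conclusion.** The point holds in a limited form. The 80% response rate is undefined: 244 is too few to approach if 20% decline and any child is lost later. The analysis rule drops children the planned model could use and selects on attendance in one arm only. At an assumed 10% to 20% loss, power is about 76% to 71% if 195 per group enter and about 84% to 80% if 244 enter. These figures rest on the back-solved SD of 7.40 cm and equal loss in both groups, and they ignore allocation by school. Neither range can be taken as the trial's power, because the text does not say which applies. The possible bias from the one-arm condition follows from the design of the rule; the documents give no basis for sizing it.

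**What to change.** - **Data analysis:** define the main mixed-model analysis set as every child with a baseline and at least one later assessment, whatever their camp attendance. Keep the present set (all three assessments, and two camps in the intervention group) as a sensitivity analysis.
- **Sample size calculation:** say what the 80% covers (participation, loss after entry, or a stated combination) and whether 244 per group counts children approached or enrolled. Tie the 80% power to 195 analysed children per group, before any design effect for schools. Do not insert 71% to 76% as the trial's power, because that range applies only if 195 per group enter.

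The cost is wording in two sections and one additional sensitivity analysis, with no extra children.

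### The stated effect size of 0.09 has no named metric and does not follow from the printed sample-size formula, which gives a standardised difference of about 0.28 at 195 per group

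*Protocol article*

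**What the plan says.** Everything relevant is in the Sample size calculation section of the protocol article. The basis is waist circumference in an earlier Malaysian study: "the mean difference of waist circumference between intervention and comparison group after the intervention programme was taken into consideration". The inputs are that "the mean change in waist circumference for intervention group after the intervention programme was 0.1 cm" and that "mean change in waist circumference for comparison group after the intervention programme was 2.2 cm". The formula is the usual one for comparing two independent means, with the significance level halved in the first Z term, so the test is two-sided. (The subscript is printed as sigma where alpha is evidently meant.)

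The result is "The calculated sample size was 195 children in intervention and comparison groups, respectively". After an adjustment for an 80% response rate, "a total of 244 children was needed for each intervention and comparison group, respectively", or 488 in all. Power is 80% and the significance level 5%. The paragraph then ends: "The small effect size of 0.09 was obtained".

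The section gives neither the SD that was put into the formula nor the kind of effect size that 0.09 is meant to be.

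**The concern.** The closing sentence reads as a by-product of the calculation just described. In a two-means calculation, an unlabelled effect size is most naturally taken as the difference divided by the SD. A value of 0.09 on that scale is far smaller than a group size near 200 can detect with 80% power, so the sentence and the sample size do not appear to belong to the same calculation.

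This paragraph is the only place where the article says what size of effect the trial can detect. Someone interpreting a null result would turn to it to judge which effects have been excluded. If the figure is wrong, or is on a scale the reader cannot identify, that judgement has no sound basis.

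**Working it through.** **Inputs, all from the Sample size calculation section.** Two-sided 5% (Z = 1.960); power 80% (Z = 0.842); mean changes 0.1 and 2.2 cm, so a difference of 2.1 cm; 195 per group before and 244 after adjustment; response rate 80%. The SD is not given. Children are treated as independent, as the printed formula does.

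**1. What reproduces.** 195 / 0.80 = 243.75, hence 244 per group and 2 × 244 = 488. The adjustment is correct.

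**2. Standardised difference implied by the group size.** The formula is n = 2·SD²·(Z₁ + Z₂)² / difference². Solved for d = difference / SD:

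d = (Z₁ + Z₂) × √(2/n)

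- n = 195: 2.802 × √(2/195) = 2.802 × 0.1013 = 0.284
- n = 244: 2.802 × √(2/244) = 2.802 × 0.0905 = 0.254

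The SD drops out: sample size, power and significance level settle d between them. With a difference of 2.1 cm, 195 per group implies SD = 2.1 / 0.284 = 7.4 cm. (An SD of 7.35 cm gives 193 and 7.45 cm gives 198.) Reading 0.09 as d would instead imply SD = 2.1 / 0.09 = 23.3 cm.

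**3. Could 0.09 be another index of the same two-group comparison?** At d = 0.284:

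| Index | Formula | Value at 195 per group | n per group for 80% power if the index were 0.09 |
|---|---|---|---|
| Standardised difference d | – | 0.284 | 1,938 |
| Cohen's f | d/2 | 0.142 | 485 |
| Correlation r | d/√(d²+4) | 0.140 | 481 |
| d squared | d² | 0.081 | 175 |
| f squared | d²/4 | 0.020 | 44 |
| Eta squared | d²/(d²+4) | 0.020 | about 40 |

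No value in the third column is 0.09, and no value in the fourth is 195. The nearest is d squared, which rounds to 0.08. A one-sided 5% test at 80% power gives d = 0.252, which is no closer. One-sided 5% with 90% power gives d squared = 0.088, but it conflicts with both the stated 80% and the two-sided formula.

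**4. Power if 0.09 is taken at face value.** Power = Φ(d × √(n/2) − 1.960).

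- 0.09 as d, n = 195: Φ(0.889 − 1.960) = Φ(−1.071) = 14%
- 0.09 as d, n = 244: Φ(0.994 − 1.960) = Φ(−0.966) = 17%
- 0.09 as f (d = 0.18), n = 195: Φ(1.777 − 1.960) = Φ(−0.183) = 43%
- 0.09 as f (d = 0.18), n = 244: Φ(1.988 − 1.960) = Φ(0.028) = 51%

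The noncentral t distribution gives nearly the same: 14.4% and 16.8% for d, 42.6% and 51.0% for f.

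**The case against.** The best defence is that the metric is unnamed and decides the conclusion. The Data analysis section plans a group-by-time model over three time points, and effect sizes for such designs are often quoted as a repeated-measures f. With 390 children (2 × 195), three measurements and zero correlation between them, 80% power for the interaction needs 390 × 3 × f² ≈ 9.6, so f ≈ √(9.6/1170) ≈ 0.091. With assumed correlations of 0.2 and 0.5 the detectable f falls to about 0.081 and 0.064. On that scale an effect of 0.09 would be within reach at the planned size. This stands as a reason not to say flatly that the trial cannot detect 0.09. It does not rescue the sentence: the article describes no such calculation, the printed formula is for two means at one comparison, and a three-measurement match to 0.09 needs a correlation near zero, which the article does not state.

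The second defence is that 0.09 feeds into nothing. The group size comes from the centimetre changes, the power and the significance level; deleting the sentence alters no number and no analysis. That is right. It limits the point to a wrong or unidentifiable reported figure.

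Third, 7.4 cm is back-solved on the assumption that 195 is correct. The SD actually used is not shown, so 7.4 cm should not be printed unchecked. This also stands.

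**Conclusion.** As written, the 0.09 does not reconcile with the calculation it closes. The formula, 195 per group, 80% power and two-sided 5% give a standardised difference of about 0.28, and no standard two-group index of that difference is 0.09. This rests only on figures in the section and on reading the misprinted subscript as alpha; it does not depend on the missing SD.

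Two stronger readings are tempting and are not supported. One is that the trial has only 14% power, or that its sensitivity is overstated about threefold (0.284 / 0.09 ≈ 3.2). That holds only if 0.09 is a standardised mean difference, which the article never says; as Cohen's f the power would be 43% to 51%, and on a repeated-measures scale 0.09 might be detectable. The other is that 195 per group is wrong. Nothing here shows that: an SD near 7.4 cm would produce it, and the SD used is not stated.

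The error is in one sentence, but that sentence carries the only stated detectable effect, so it should be corrected.

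**What to change.** Replace the closing sentence with the standardised difference the calculation delivers, and give the SD. For example: *The assumed difference of 2.1 cm with an SD of [value used] cm corresponds to a standardised difference of about 0.28.* Take the SD from the source calculation. If it is close to 7.4 cm, the 195 is confirmed; if it is not, the group size itself needs to be recalculated.

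If the authors wish to keep 0.09, they should name the metric and show the calculation behind it, including any assumed correlation between measurements. If it turns out to be the expected standardised difference, the 80% must be restated: about 14% at 195 per group and 17% at 244 under the printed formula.

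The cost is a sentence or two. Provided the SD checks out, the sample size, design and analysis are unchanged; the only consequence is that a reader who took 0.09 as a standardised difference will see a larger minimum detectable effect.
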